**Figure 1 F1:**
[figure not shown]
**Major components* of QUIT-PRIMO provider-patient informatics intervention**. * All components are supported by repeated, targeted email reminders designed to prompt participation and cue increased smoking cessation. Emails will invite enrolled smokers, provide motivational and educational messages to enrolled smokers, notify providers of new web reports, and alert providers to new messages from patients. A proactive Help Desk will also be available as part of the intervention.

#### ReferaSmoker.org implementation program

After practices are enrolled, we will then schedule and conduct individualized telephone trainings with two implementation coordinators (physicians, nurses, or other staff) chosen at each practice. We chose two implementation coordinators per practice because of high rates of turnover of office staff in our prior experiences. Two coordinators can provide each other backup and further enhance use of ReferaSmoker.org. Using an academic detailing approach, our study team will walk the implementation coordinators through the ReferaSmoker website, including initial registration, and practice e-referring a test patient.

Using motivational interviewing, we will work with the implementation coordinators to identify barriers and strategize solutions to enhance participation. Implementation coordinators will set a goal for number of referrals per week based on their practice volume. Implementation coordinators will be trained on registering other providers in the practice into the system.

Based on pilot testing and focus groups, we have identified specific incentives, including provision of continuing education credits to participating providers and a $1,000 per practice "implementation budget" for completing training and referring their first 20 smokers. Proactive booster calls will be scheduled one month after initial registration to assess progress, respond to any questions, and continue to motivate participation.

#### The practice-level comparison

The practice-comparison referral process ends at the information prescriptions. Comparison practices will be enrolled in the same manner and will participate in the implementation program training calls. Randomization will occur on the calls once registration is complete, as further described below. The ReferaSmoker.org portal changes dynamically based on the randomization status of the practice, and comparison practices will only receive the supportive educational materials (Figure 1, ReferaSmoker #3). Comparison practices do not have access to the e-referral system, the practice feedback dashboard, or the secure messaging system.

As noted, comparison practices are provided preprinted pads of information prescriptions, exactly like those the intervention practice received, save one detail. There is no space for the patient email because control providers will not use the e-referral system (see Additional File 2, Appendix 2). Smokers will be provided half the information prescriptions, with the Decide2Quit.org address, just as with the intervention practices. All other components of the implementation program, motivational interviewing and goal-setting, incentives, and booster calls are kept constant across the two arms. Practices randomized to the comparison do receive a more limited training, focusing on the paper information prescriptions.

#### Decide2Quit.org, the patient-level intervention

Providers refer patients to Decide2Quit.org by paper prescription in the comparison group or by paper plus e-referral in the intervention group. Patients e-referred to Decide2Quit.org will receive reminder emails (two per week for four weeks) as cues to participation.

Patients who follow the referral and register with Decide2Quit.org will complete an online consent form and a baseline survey, including assessment of their readiness to quit smoking. This baseline data will be used to tailor the website to the individual.

Once registration is complete, smokers from both intervention and control practices will be further randomized. This within-practice randomization will allow smokers to receive one of two versions of Decide2Quit.org: a standard Decide2Quit.org or an augmented version of Decide2Quit.org (Table 1).

**Table 1 T1:** Major components of Decide2Quit.org

Component	Description
MyMail^a^	Receive messages from a tobacco treatment specialist

Our Advice^a^	Receive encouraging email messages from experts; messages tailored to stage of change

Your Online Community^a^	View messages and dialogue from smokers and ex-smokers through a resource website

My Health Risks^b^	Learn about specific health risks, including physical symptoms and harmful chemicals

Thinking About Quitting^b^	Helpful ideas and motivational recommendations (*e.g*., interactive calculators assessing triggers, decisional balance)

Family Tools^b^	How to get help from your family, deal with nagging, learn what kids think about smoking

Healthcare Provider Tools^b^	How to include your healthcare provider in your quit smoking plan

The Library^b^	Download articles and helpful tools about smoking cessation and smoking treatments

Web Resources^b^	Valuable additional websites for smokers

^a^These components are available only to the augmented Decide2Quit.org intervention; ^b^Standard components available to all smokers registered to Decide2Quit.org, both those randomized to standard version and those randomized to augmented version.

The standard comparison Decide2Quit.org includes a library of information about quitting smoking, including educational content about talking to a doctor about quitting smoking and detailed information on medications and behavioral treatments. The system also includes content about seeking help from friends and family, a chemicals-in-smoking matching game, and a decisional-balance "what will I have to overcome" calculator with individualized feedback. Smokers can complete a personalized "Quit Plan" that they can print and share with their provider.

The augmented Decide2Quit.org intervention includes all the components of the standard intervention plus (a) pushed motivational emails tailored to readiness to quit and designed to motivate cessation and market the Decide2Quit.org intervention; (b) secure asynchronous messaging with a personal advisor, a trained tobacco treatment specialist; and (c) an online support group community (Table 1).

Thus, our study is a cluster-randomized trial, with patients clustered at the practice level, and a subsequent, within-practice, patient-level randomization (Figure 2). This is further detailed under *Randomization *below.

**Figure 2 F2:**
[figure not shown]
**Enrollment and randomization strategy**.

### Objectives

As conceptualized for one patient in an example practice depicted in Figure 3, the intervention is designed to have a sequence of effects on the process of care within each clinical microsystem. The system has the potential to impact provider behavior (nurses and physicians), processes of care, and patient behavior. Thus, we have designed our main evaluation to assess several key areas of influence, which we have abbreviated as Refer → Go → Quit. To evaluate the impact of the provider and patient intervention, we have proposed the following three hypotheses:

**Figure 3 F3:**
[figure not shown]
**How the integrated QUIT-PRIMO is conceptualized to improve processes of care (5 *A*s) and increase smoking cessation: use of the clinical microsystem intervention over time by one example practice and one patient**. **A1: Ask**--ReferaSmoker sends email prompts to providers reminding them of the importance of smoking cessation; provider downloads printable chart stickers, etc., to increase systematic screening by nurses. **A2: Advise--**ReferaSmoker materials provide additional knowledge to providers on strong advice; provider advises patient. **A3: Assess--**Provider explains content of Decide2Quit and assesses willingness of patient to use system and to quit. **A4: Assist--**Patient agrees to be recruited and nurse enters patient email into ReferaSmoker online portal and patient is enrolled into the system. Decide2Quit sends email reminders to the patient. Patient uses system and talks to family because of the motivational messages. **A4: Assist--**Patient engages in the online support group, shares his quitting experiences and finds others with similar experiences, posts a question online, and interacts with other smokers trying to quit. **A4: Assist--**Patient selects a tobacco treatment specialist (TTS) and posts a question to her using the MyMail feature of the system. The TTS responds with helpful suggestions, and the patient returns to the system to read her responses. **A4: Assist--**Patient continuously receives tailored "advice" emails from the system. Emails are from experts and peers. **A5: Arrange--**Nurse (and/or physician) reviews reports of patient use and follows up. Nurse sends a template-driven email message encouraging use of the system and offering treatment. **A4: (more) Assist**--Patient returns to Decide2Quit repeatedly, is increasingly motivated, requests treatments → quits.

Hypothesis 1 (Refer): More patients will be **Refer**red to the Decide2Quit self-management resource website in the QUIT-PRIMO e-referral practices compared with information prescription practices.

Hypothesis 2 (Go): The proportion of referred patients who **Go **to the patient self-management website due to the QUIT-PRIMO practice proactive e-referrals will be greater compared with the paper information-prescription practices.

Hypothesis 3 (Quit): The proportion of referred smokers who **Quit **at six months will be greater among those in the augmented Decide2Quit.org intervention compared with the standard intervention.

### Outcomes

For our three hypotheses, we have three primary outcome variables (*i.e*., Refer, Go, Quit). For the primary analysis for hypothesis 1, the outcome will be the number of smokers referred from each group transformed into an average count per month by dividing the total by the length of time in months from the practice's first referral. As discussed above, in both arms, practices will use paper information prescriptions. The leave-behind part of the information prescription (see Appendix 1) will allow a consistent measure of referrals. In the QUIT-PRIMO intervention, the server will track the number of electronic referrals, allowing us to compare rates of referral based on paper and server in the intervention arm.

For hypothesis 2, our outcome will be the proportion of those referred who go to the website. Our interest in hypothesis 2, expressed as a proportion, will be the proportion of patients referred who log on, or "Go," to the website (% who go = number who visit/number referred). The number of smokers who visit will be recorded by the Decide2Quit system, linking each visitor to their primary care provider at initial registration. The number referred is continuously registered directly by the leave-behind referral receipts of the information prescriptions.

For hypothesis 3, we will define the outcome in two ways. In both approaches, the numerator will be the number of patients who report cessation at six-month follow-up calls. In our primary intent-to-treat analysis, the denominator will be all smokers who are referred (the same denominator used in hypothesis 2), estimating a population effect. This represents a conservative assessment since we assume that many patients will not go, and for the purposes of analyses, we will assume that these patients will not have quit. As a secondary analysis, we will assign the denominator as the number of patients who go to the website. For this secondary outcome, consistent with current guidelines for smoking cessation trials, we will assume that patients who are lost to follow-up, including those who go and do not agree to follow-up, are smokers [34].

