## Background

Tobacco use is the number one behavioral health problem and number one preventable cause of death [1-5]. Interventions to reduce smoking have most frequently targeted patients. Patient self-management interventions for smoking cessation include mass dissemination of tobacco cessation self-help materials, computer-tailored printouts, interactive voice response systems, and more recently, "quitlines" and smoking cessation websites [3,6-13]. Unfortunately, self-management interventions for smoking cessation have been underutilized. Studies of quitlines note that as little as 3.5% of adult smokers call per year [14]. Because the majority of smokers (70%) see a healthcare provider at least once per year [15], physician referrals could greatly increase use of publicly available self-management interventions for smoking.

Quality improvement and implementation interventions have tried to change processes of care or provider behavior related to tobacco control with some success. Brief clinical interventions, based on tobacco use screening and brief, structured cessation advice from a provider, have been documented to improve patient cessation rates [15-18]. The current US Department of Health and Human Services clinical practice guideline entitled "Treating Tobacco Use and Dependence" provides a summary of evidence-based recommendations [5]. The current guideline includes a framework for structured, brief clinical interventions using the "5 *A*s" of counseling:

1. Ask: Identify and document tobacco use status for every patient at every visit.

2. Advise: In a clear, strong, and personalized manner, urge every tobacco user to quit.

3. Assess: Is the tobacco user willing to make a quit attempt at this time?

4. Assist: Refer to resources and provide pharmacotherapy and counseling.

5. Arrange: Schedule follow-up contact, preferably within the first week after the quit date.

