#### ReferaSmoker.org, the practice-level intervention

Intervention practices will be provided preprinted pads of "information prescriptions" with their office information, a space for the provider to sign, and the smoking cessation website address (Decide2Quit.org). The information prescriptions are perforated; half will be retained by the practice (including the patient email to be used for e-referral) and half will be provided to the patient (see Additional File 1, Appendix 1). Practices will then use this patient email collection to e-refer them through ReferaSmoker.org. The core of the ReferaSmoker.org provider portal is a secure sockets layer (SSL) encrypted web form where providers can enter patients' email addresses into the system if they agree to be referred (Figure 1). The form has been designed to be easily completed by nursing or front office staff as the patient is discharged from the visit. Online referrals through the SSL form will be tracked by the server. The practice-reports function will provide feedback reports to providers on their patients' progress and their practice's referral rates. These feedback reports will act as a proximal outcome, where providers of all types can actually observe the impact of their efforts. To maximize the use of ReferaSmoker.org, we also provide supportive sub modules designed to prompt providers to use the system and maximize their smoking cessation activities (Figure 1, ReferaSmoker #3).

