### Analysis

The mean number of referrals per month will be compared by study group using a two-sided *t*-test, employing Satterthwaite's approximation if the variances are substantially different. We will also examine the distribution of the referrals per month by study group and will use the two-sided Wilcoxon test if they appear non-Gaussian. We will assess the adequacy of randomization on characteristics of the practice that might influence referral rates. We will have data from an administrative database (size of practice, number of providers and staff) and provider reports of proportion of smokers in the practice. We will also conduct adjusted (using Poisson or negative binomial models based on distribution) analyses accounting for these factors.

For hypothesis 2, whether or not a patient goes will be considered a dichotomous outcome in a patient-level analysis. The main patient-level analysis will use a generalized linear model with a logit link to evaluate whether a referred smoker goes to the patient website. As this hypothesis represents a cluster-randomized trial, because each website links patients back to their practice, we will use generalized estimating equation (GEE) methods to account for clustering within practices.

For hypothesis 3, patients will be randomized within practices to standard Decide2Quit and augmented Decide2Quit. Because we are comparing rates in all instances between the standard Decide2Quit system and the augmented Decide2Quit, we will use a two-group chi-square test of equal proportions to test the statistical difference between the quit rates. We will next use a generalized linear model with a logit link to model tobacco cessation by treatment assignment adjusted for baseline readiness to change as entered into the website by the patient.

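### Refer and Go are defined per smoker but counted from referral slips, so repeat slips lower Go and Quit and, if the intervention raises referral per visit, inflate the Refer ratio and bias Go against hypothesis 2

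*Protocol article*

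**What the plan says.** Hypothesis 1 (Objectives) is about how many patients are referred, and hypothesis 2 about the proportion of referred patients who go to the website. In Outcomes the hypothesis 1 unit is the smoker: "the outcome will be the number of smokers referred from each group transformed into an average count per month".

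The instrument is the paper slip. Outcomes states: "The leave-behind part of the information prescription (see Appendix 1) will allow a consistent measure of referrals". For the Go denominator: "The number referred is continuously registered directly by the leave-behind referral receipts of the information prescriptions". The primary Quit analysis takes over that count: "the denominator will be all smokers who are referred (the same denominator used in hypothesis 2".

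The Go numerator is a count of persons: "The number of smokers who visit will be recorded by the Decide2Quit system, linking each visitor to their primary care provider at initial registration". The Analysis section keeps that unit: "whether or not a patient goes will be considered a dichotomous outcome in a patient-level analysis".

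On what the slips carry, the section on the practice-level intervention describes office information, a signature space and the website address, and says that "half will be retained by the practice (including the patient email to be used for e-referral". The section on the practice-level comparison says that its pad differs in one respect only: it has no space for the email. No other patient identifier is described for either pad. Appendices 1 and 2, which show the forms, are not available here.

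**The concern.** A slip is issued per referral and a registration is made per person. A smoker handed slips at two visits adds two to the Refer count and to the Go and primary Quit denominators, but can add only one to the Go numerator. The section gives no rule that ties a smoker to one slip.

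Three primary outcomes use this count. Repeats lower the absolute Go and Quit proportions in any case. They distort the comparison between practice arms when one arm repeats more than the other. That follows if the intervention succeeds in raising referral per visit, because a higher chance of referral at each visit produces more second and third slips.

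A later analysis plan could choose a counting rule, but it could not recover an identity that the comparison pad did not collect. On the content described, the counting unit has to be settled on the pad.

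**Working it through.** **Inputs (Sample size, Table 2).** 3,000 visits per practice over two years; 22% smokers; 24% vs 12% referred; 40% vs 20% of those referred go. The table's title speaks of patients, but its first row and footnote say visits. I take the base as visits.

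**Reproducing the plan's figures.** 3,000 × 0.22 = 660. Referred: 660 × 0.24 = 158.4 and 660 × 0.12 = 79.2, printed as 158 and 79. Go: 158.4 × 0.40 = 63.4 and 79.2 × 0.20 = 15.8, printed as 63 and 16. The table reproduces, on a visit base.

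**Effect of repeats.** Let k be the slips per distinct smoker in an arm.
- Slip count = distinct smokers × k.
- Slip-based Go = true Go ÷ k. The primary Quit proportion is divided by k in the same way.

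**Equal repeats.** With k = 1.25 in both arms, Go reads 0.40/1.25 = 32% vs 0.20/1.25 = 16%. The ratio stays at 2.00, and so does the Refer ratio. Only the absolute proportions fall.

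**Unequal repeats.** Assume each smoker makes v visits in two years and is referred at each with probability r (0.24 or 0.12), independently of earlier referrals. Then:
- slips = 660 × r
- distinct smokers = (660/v) × [1 − (1 − r)^v]
- k = v × r ÷ [1 − (1 − r)^v]

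For v = 2: distinct = 330 × (1 − 0.76²) = 139.4 and 330 × (1 − 0.88²) = 74.4; k = 0.48/0.4224 = 1.136 and 0.24/0.2256 = 1.064; Go = 0.40/1.136 = 35.2% and 0.20/1.064 = 18.8%.

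| v (assumed) | Distinct smokers referred | Ratio in smokers | Ratio in slips | k | Go as read, true 40% vs 20% | Go ratio, true 2.00 |
|---|---|---|---|---|---|---|
| 1 | 158 vs 79 | 2.00 | 2.00 | 1.00, 1.00 | 40% vs 20% | 2.00 |
| 2 | 139 vs 74 | 1.87 | 2.00 | 1.14, 1.06 | 35.2% vs 18.8% | 1.87 |
| 3 | 123 vs 70 | 1.76 | 2.00 | 1.28, 1.13 | 31.2% vs 17.7% | 1.76 |
| 4 | 110 vs 66 | 1.67 | 2.00 | 1.44, 1.20 | 27.8% vs 16.7% | 1.67 |

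The true 20-point Go difference would read as 35.2 − 18.8 = 16.4 points at v = 2 and 27.8 − 16.7 = 11.1 points at v = 4.

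**If repeats were removed in the intervention arm only.** Take no true effect, with 12% referral per visit in both arms and equal Go. The Refer ratio becomes 1/k and the Go ratio k, where k is the comparison arm's value. For v = 2 to 4 that is a Refer ratio of 0.94 to 0.83 and a Go ratio of 1.06 to 1.20. Counting alone would create a Go advantage.

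**The case against.** **The plan counts slips alike.** Outcomes gives the server count one role, a paper-versus-server comparison within the intervention arm. A reader might infer that repeats will be removed by email in that arm alone, so that Go is tilted towards hypothesis 2. The documents do not support this: nothing in them proposes it. As written, the bias in Go runs against hypothesis 2.

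**The evidence for repeats is thin.** A reader might take "Identify and document tobacco use status for every patient at every visit" as an instruction to refer at each visit. It is background on the guideline's Ask step. Referral belongs to Assist, which the Background says is carried out less often. The independence assumption in the table is also close to a worst case, since staff may be less likely to give a second slip to a smoker already referred. Both points stand, and the size must be read accordingly.

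**Both arms are prompted.** A reader might infer that only intervention practices are prompted to refer again. The supportive materials labelled ReferaSmoker #3 go to both arms, and goal-setting, incentives and booster calls are held constant. What differs includes the feedback dashboard on referral rates. Unequal repeats therefore rest on the intervention raising referral per visit, not on one-sided prompting.

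**The forms are not shown.** A name or chart number on both stubs would allow repeats to be removed symmetrically. That would make the repair easier, but a counting rule would still be needed.

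**A journal article may leave a duplicate rule to the full documents.** This is true of the rule. It does not settle the pad: on the content described, a later rule would have nothing to work with in the comparison arm.

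**Conclusion.** The point holds as a mismatch of units. Hypotheses 1 and 2 concern smokers; the Refer outcome and the Go and primary Quit denominators count slips; the Go numerator counts persons. Repeats lower the absolute Go and Quit proportions whether or not they are equal between arms. The Refer and Go ratios are affected only if repeat rates differ. If the intervention arm repeats more, Refer is overstated as a count of smokers and Go is understated in relative terms.

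The size rests on an assumed number of visits per smoker, on independent referral at each visit, and on reading Table 2 as visits. Over 2 to 4 visits, the Refer ratio in smokers is 1.87 to 1.67 where slips show 2.00, and the Go ratio reads 1.87 to 1.67 against a true 2.00. With one slip per smoker the effect is nil. The statement that repeats cannot be recognised in the comparison arm depends on the slip content as described, with the appendices unseen. This is a cheap improvement worth making, not evidence that the comparison is invalid.

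**What to change.** - Print the same tick box, *first referral / already referred in this study*, on the retained half of both pads. If an identifier already stands on both stubs, use that instead.
- Count only first referrals for the hypothesis 1 outcome and for the hypothesis 2 and primary hypothesis 3 denominators.
- Report total slips per month as a secondary process measure.
- State that one counting rule applies in both arms, and that repeats will not be removed by email in the intervention arm alone.

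The cost is one printed box and one sentence of counting rule. The tick depends on staff and patient recall, so some misclassification will remain. The practice payment tied to the first 20 smokers referred may favour ticking *first*. The method and the incentive are the same in both arms.

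### The retained slip that counts referrals differs by arm in content and use, and is cross-checked in one arm only, so differential slip retention could bias hypotheses 1 and 2 unseen

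*Protocol article*

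**What the plan says.** For hypothesis 1, "the outcome will be the number of smokers referred from each group transformed into an average count per month" (Outcomes). Paper prescriptions are used in both arms, and the protocol relies on the half kept by the practice: "The leave-behind part of the information prescription (see Appendix 1) will allow a consistent measure of referrals". Only Appendix 1, the intervention form, is cited there.

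The same count is the denominator for hypothesis 2: "The number referred is continuously registered directly by the leave-behind referral receipts of the information prescriptions". It is also the denominator of the primary analysis of hypothesis 3.

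The section on the practice-level intervention says of the intervention pads that "half will be retained by the practice (including the patient email to be used for e-referral", and then "Practices will then use this patient email collection to e-refer them through ReferaSmoker.org". The section on the practice-level comparison says of the other pads: "There is no space for the patient email because control providers will not use the e-referral system". It adds: "Comparison practices do not have access to the e-referral system, the practice feedback dashboard, or the secure messaging system".

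A server count of referrals exists for intervention practices only, "allowing us to compare rates of referral based on paper and server in the intervention arm" (Outcomes).

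**The concern.** A count that serves as a primary outcome should be captured in the same way whichever arm a practice is in. Here the randomised treatment changes what the slip is for. An intervention practice needs the retained half to do its e-referral work, and that work feeds its reports. A comparison practice keeps the half only as a record of referral. The slips also differ in content. An email lets repeat slips for one smoker be recognised, at least for patients who give one. The text describes no such identifier on the comparison slip, although the outcome is a number of smokers.

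If retention differs, hypothesis 1 can show a difference in referral where there is only a difference in record-keeping. The hypothesis 2 denominator moves with it. The paper-versus-server comparison could expose lost slips in the intervention arm, but nothing described would expose them in the comparison arm. The analyses named under Analysis for hypothesis 1 (t-test, Wilcoxon test, adjusted Poisson or negative binomial model) all take the slip count as given, so none of them repairs this.

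**Working it through.** **Step 1. The plan's own figures (Sample size, Table 2).** Smokers: 3,000 × 0.22 = 660. Referred: 660 × 0.24 = 158.4 (intervention) and 660 × 0.12 = 79.2 (control). Go: 158.4 × 0.40 = 63.4 and 79.2 × 0.20 = 15.8. These reproduce the printed 158, 79, 63 and 16.

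**Step 2. Assumptions, because the documents give no figure.**
- Share of issued slips retained: r_I = 0.95 in the intervention arm; r_C = 0.90, 0.85 or 0.75 in the comparison arm.
- Between-practice coefficient of variation (CV): 0.5 to 1.0.
- 80 practices per arm (160 in total; the allocation ratio is not stated), two-sided alpha 0.05, and equal observation time, so that totals and monthly averages give the same test.

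**Step 3. Hypothesis 1 with no true difference.** Both arms truly refer m = 79.2 per practice. The apparent ratio is r_I / r_C. Practice counts were simulated as gamma-Poisson, thinned by retention and compared with an unequal-variance t-test (4,000 runs per setting).

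| r_C | Apparent ratio | False positives, CV 0.5 | False positives, CV 1.0 |
|---|---|---|---|
| 0.90 | 0.95/0.90 = 1.06 | about 10% | about 6% |
| 0.85 | 0.95/0.85 = 1.12 | about 27% | about 11% |
| 0.75 | 0.95/0.75 = 1.27 | about 83% | about 31% |

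A repeat with 6,000 runs agreed within simulation error (10%, 28%, 82%; 6%, 10%, 30%) and gave about 5% when retention was equal.

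One cell by hand, r_C = 0.75 and CV 0.5. The observed means are 75.24 and 59.40, a difference of 15.84. The variance of a practice count is (CV × mean)² + mean, which gives 1,415.3 + 75.2 = 1,490.5 and 882.1 + 59.4 = 941.5. The standard error is √[(1,490.5 + 941.5)/80] = 5.51, so the standardised difference is 2.87. The rejection probability is about Φ(2.87 − 1.96) = Φ(0.91), or 82%.

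**Step 4. A wider range.** Let c be comparison retention relative to intervention retention. A normal approximation without the Poisson term, again with no true difference, gives:
- c = 0.9: ratio 1.11, rejection 10% to 26%
- c = 0.8: ratio 1.25, rejection 29% to 80%
- c = 0.5: ratio 2.0, rejection 98% to 100%

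In each range the lower value is for CV 1.0 and the higher for CV 0.5. Only a 50% relative loss would create the whole planned 2:1 contrast.

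**Step 5. Hypothesis 2 at the planned true rates.** Visitors are recorded by the website, so slip loss shrinks only the denominator, and the apparent rate is the true rate divided by retention. With r_I = 0.95 and r_C = 0.75, the rates are 0.40/0.95 = 42.1% and 0.20/0.75 = 26.7%. The odds ratio is (0.421/0.579)/(0.267/0.733) = 2.0, against a true (0.40/0.60)/(0.20/0.80) = 2.67.

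**Step 6. The other direction.** With r_I = 0.75 and r_C = 0.95, the apparent hypothesis 1 ratio is 0.75/0.95 = 0.79. The Go rates read 0.40/0.75 = 53.3% and 0.20/0.95 = 21.1%, an odds ratio of (0.533/0.467)/(0.211/0.789) = 4.3.

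**Step 7. Repeat slips.** Undetected repeats in the comparison arm inflate its count. That works against the intervention on hypothesis 1 and lowers the comparison Go rate on hypothesis 2, the opposite of losing slips there.

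**The case against.** The best defence is that the protocol claims less than this point reads into it. In context, the sentence explains why paper, which exists in both arms, is used instead of a server count that exists in one. The pads are described as identical apart from the email space. The retained halves are called receipts that register referrals, so the comparison half has a stated recording function. Both arms have the same goal-setting, booster calls and $1,000 payment tied to training and the first 20 referrals. Paper is the only referral record described for comparison practices, which is a plausible reason to keep it.

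Much of this stands. A reader might infer that the comparison half is a stub nobody uses, or that the outcome is certainly distorted in the intervention's favour. The documents support neither. No retention rate is given for either arm, and the direction is open. Intervention slips may be discarded once the email is entered, or bypassed if staff type the address straight into the portal, as the Background describes. Nor would modest loss explain a planned 2:1 contrast. On hypothesis 2, loss of comparison slips works against the intervention, so it would not create a false positive there.

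Both forms are in appendices that are not shown. The remark about identifiers therefore rests on the assumption that the comparison form adds none.

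The defence does not remove the arm difference that the protocol itself describes. The one detail in which the pads differ is what gives the slip a working use in one arm only. The documents do not say that slips prove the 20 paid referrals. Twenty is also about a quarter of the 79 expected (20/79 = 25%), so the payment gives no reason to keep later slips. The uncertain direction means that retention has to be measured; it does not show that retention is equal.

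**Conclusion.** The concern holds as a risk of undetected differential capture in a primary outcome, not as a demonstrated bias. Slip content and role differ by arm, and only the intervention arm has a second count. The measure should therefore not be called consistent without a count that works the same way in both arms.

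Under the assumptions in the working, a retention gap of 5 to 20 percentage points raises the hypothesis 1 false-positive rate from 5% to between 6% and 83%, and at the 20-point gap it moves the comparison Go rate from 20% to 26.7%. The upper figure is the extreme corner (75% against 95% retention, CV 0.5); at CV 1.0 the same gap gives about 31%. If intervention slips are the ones lost, both biases reverse. The primary hypothesis 3 denominator is the same count and inherits the problem; its size there was not worked out.

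It would go too far to say that neither result can be told apart from record-keeping. A true 2:1 referral ratio would remain visible under the modest losses illustrated here. The change is still worth making, because it is cheap and no later analysis can recover slips that were not kept.

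**What to change.** - Print sequential serial numbers on the pads in both arms.
- Define the hypothesis 1 count and the hypothesis 2 denominator as prescriptions issued: serial numbers used, reconciled against unused and spoiled slips at re-supply or close-out.
- Put the same repeat-referral tick box on both forms, so that smokers rather than slips can be counted in both arms.
- Report retained halves divided by prescriptions issued, by arm.
- Do not make entry of the serial number at registration a condition for counting Go. E-referred patients are reached by email and may register without the slip, so such a rule could fail more often in the intervention arm.

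The cost is numbered printing and a pad reconciliation. No extra practices or patients are needed.
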